## Abstract

**Background:**

Information and communication technologies (ICT) have become one of the main pathways to the new paradigm of increased self-management of chronic conditions such as alcohol dependence. Validation of some mobile phone apps has begun, while validation of many others is forthcoming.

**Objective:**

To describe the protocol for validation of a new app called SIDEAL (an acronym of the Spanish name “Soporte Innovador a la persona con DEpendencia del ALcohol,” or innovative support for people with alcohol dependence).

**Methods:**

The project consists of 3 complementary, consecutive studies, including a pilot feasibility study, a qualitative study using focus groups, and, finally, a randomized controlled trial where patients will be randomized to standard treatment or standard treatment plus SIDEAL. During the pilot study, feasibility, usability, and acceptance by users will be the main outcomes explored. An electronic questionnaire will be sent to patients asking for their opinions. Focus groups will be the next step, after which improvements and refinements will be implemented in the app. During the final phase, consumption variables (heavy drinking days per month, mean standard drinks per day) will be investigated, in order to test app efficacy.

**Results:**

Because of the encouraging results with previous similar apps, we expect patients to widely accept and incorporate SIDEAL into their therapeutic options. Significant reductions in drinking-related variables are also expected. The pilot study has concluded with the inclusion of 29 patients. Results are expected to be available soon (expected mid-2016).

**Conclusions:**

SIDEAL may represent a useful, reliable, effective, and efficient tool to complement therapeutic options available to both patients and professionals.

## Introduction

According to the World Health Organization [1], alcohol is the third largest contributor to the global burden of disease in developed countries, accounting for massive costs at both the individual and society level. Alcohol dependence, now formally labeled severe alcohol use disorder, is a medical, chronic, relapsing disease. In Spain, for example, it accounts for nearly 75% of the total burden of disease attributable to alcohol [2]. Because of its chronic, relapsing-remitting nature and high costs, there is a strong need to develop new ways to provide continuous care.

Information and communication technologies (ICT) could offer an approach to the addiction field through a new paradigm of increased self-management. Moreover, technology has the potential to provide continuous personalized care at a fraction of the cost of standard care. Existing evidence supports the suitability of chronic diseases as a target for technological assistance, to improve quality of life and reduce health care costs [3]. These facts have not gone unnoticed by national and international institutions, which are now clearly supporting and encouraging the development of such technologies. A clear example is the Horizon 2020 initiative of the European Commission, with an approximate budget for ICT-related projects of €560 million.

Intelligent mobile phones, or *smartphones* are currently widely used in Spain (4). Besides the usual telephone service, they offer computer-like functions with advanced software capabilities. Their portability, ease-of-use, and ubiquity make them excellent tools to enhance the management of chronic conditions. A new horizon of interactions between health care services and users with mobile phones as mediators can be envisioned. The range of possibilities includes scheduling visits for psychoeducation, monitoring, brief interventions, and biometric assessments.

A multitude of mobile apps specifically focusing on alcohol are currently available in the software market. However, recent reviews point out that a majority of them encourage drinking, while a smaller number support the reduction of problematic drinking. However, little research supporting their use is available [4,5]. One randomized, controlled trial was conducted, and encouraging results were reported [6]. Additional trials are expected in the near future, in a growing effort to apply scientific standards to this continuously and rapidly changing new area of ICT.

Recent publications [4,7-9] identified two key elements critical to the efficacy of apps in the management of chronic diseases. These include ongoing monitoring and use of push technology (which provides sustained proactivity). Other success-conditioning factors are usability, institutional support, expert endorsement, and individualized adjustment or tailoring. It is also strongly urged that these apps be evaluated using the scientific method, which will allow for the implementation of apps based not only on their usability, but also on their validity, effectiveness, and efficiency.

Mobile phones have been suggested to be suitable platforms for the management of alcohol use disorders via apps that integrate different functions. These include skills training, motivation enhancement, psychoeducation, social support, relapse prevention, and reminders (medical visits, medication schedules, health events). In addition, technology allows for the implementation of a system for continuous monitoring and ecological momentary assessment ("in the moment") [4]. The information gathered can then be displayed to the user (thus providing feedback) in an attractive way, facilitating modulation of the problematic behavior. All these features and functions therefore allow not only for simple and efficient collection of information, but also for the combination of this information with other functions to potentially encourage motivation, decrease problems associated with consumption, and even support relapse prevention [10].

The SIDEAL project (an acronym of the Spanish name “*Soporte Innovador a la persona con DEpendencia del ALcohol*,” or innovative support for people with alcohol dependence) was undertaken in this context. SIDEAL is a public-private collaboration of Lundbeck Spain SA, Pulso Ediciones, SL, the Subdirectorate of Drug Addictions of the Catalonia regional government, and the Addictions Unit of the Clinic Hospital of Barcelona. A Web-based app system has been developed to support alcohol-dependent patients. This paper reports its theoretical basis and development process, as well as the protocols of the different studies that will be conducted to validate its usability and efficacy.

## Methods

### Theoretical Basis and Patient Implementation

The main source of theoretical guidance for SIDEAL comes from motivational interviewing (MI) principles [11]. MI is intended to help people move through the stages of change [12] in a nonjudgmental, facilitative manner. Although it has a directive, goal-oriented style, it is respectful of patients’ goals. MI also encourages an individual, tailored approach for each patient. Therefore, SIDEAL is respectful of patients’ goals, and allows for tailoring of the app according to their preferences. Other principles adopted in the development of the app include design simplicity, noninvasive proactivity, privacy, professional endorsement and support, and adjustment to individual needs. An increasing number of guidelines and recommendations for developing apps aimed at behavioral change [13,14] are also currently available and continue to be useful as a source of practical guidance.

While other apps currently being validated, such as the Location-Based Monitoring and Intervention for Alcohol Use Disorders (LBMI-A) [8], have been designed as stand-alone, self-administered, independent treatments for alcohol patients, the purpose of SIDEAL is to become a tool that both patients and professionals can incorporate into their therapeutic armamentarium. Although the app may work as a stand-alone option, we think that it is best used under the principles of shared information and decision-making between patients and professionals. All information produced by users is transferred to a Web system to which professionals have access. In order to respect patients’ privacy, however, users always have to proactively allow the information to be transferred to the Web by clicking a specific button in the app.

The app is currently available free of charge in the main app markets (ie, Apple Store and Google Play). However, to create a user account and tailor and personalize features, patients should have an initial visit with a professional, during which both the patient and professional will configure the user’s account via the Web system. For example, the main treatment goal will be set (choosing between complete abstinence and reduction). If reduction is selected, a desired daily consumption limit will also be set. If a patient is taking any specific medication, this will also be recorded in the user’s account. Based on patient preferences, professionals will be able to select which psychoeducational text message (short message service, SMS) the user will receive on a weekly basis.

### SIDEAL Development Process

The development and testing phases of the Web-based app system were conducted from September 2013 to December 2014 by a collaborative team of specialists in addictions (psychiatrists) and software engineers, as well as graphic designers and project managers, with previous experience in the development of patient support software. All user requirements, functions, and software design were first established, and the installation (soft and hard), operational key functions, and performance requirements were subsequently tested to evaluate the entire system.

In addition to compliance with security and privacy rules, relevant app requirements and functionalities include easy-to-use functions for selecting a program (reduction or abstinence); recording daily alcohol consumption (standard units); graphically monitoring standard units in reference to the established limit; accessing educational information; and displaying a telephone help line (public or private). For users monitored by a physician who previously created a user profile for them through the Web interface, additional app functions were included for downloading consumption goals and prescribed therapies from the dedicated professional Web interface; recording and monitoring treatment adherence; receiving automated personalized feedback (weekly via the app); receiving one general piece of advice weekly (a text message selected at random from a pool of 50); and receiving surveys for users to provide feedback.

All 50 text messages were selected and reviewed by the investigator’s panel based on best practice standards and consensus. Updated published educational information was used.

### SIDEAL Functionalities

The different “modules” or functionalities included in the app may be accessed in parallel, with no restrictions, in contrast to the stepwise approach implemented in other apps. Figure 1 shows the initial screen, where all functionalities may be accessed.

**Figure 1 figure1:**
[figure not shown]
Initial screen.

#### Consumption Records

Patients record alcohol consumption using icons representing alcoholic drinks. The system automatically converts this information into standard units and displays it in a graphic where the agreed limit is also displayed. The user can set reminders that will appear when consumption limits are exceeded. Consumption may be introduced gradually throughout the day, all at once, or even on subsequent days using the calendar function, which allows for the selection of previous dates. The system also allows patients to record that no consumption has occurred during the day. Figure 2 shows a consumption register screen.

**Figure 2 figure2:**
[figure not shown]
Consumption register.

#### Drug Adherence Record

If the patient is receiving an alcohol-specific drug treatment, the system also allows for recording daily drug compliance. The system automatically computes percent drug adherence. Figure 3 shows one of the screens of this module.

**Figure 3 figure3:**
[figure not shown]
Pharmacological adherence register.

#### Calendar

Patients can enter the dates of visits to different health care professionals. The system will produce reminders with push technology to remind patients of their scheduled visits. Figure 4 presents a screen showing this function.

**Figure 4 figure4:**
[figure not shown]
Calendar.

#### Medical Information and Psychoeducation About the Disease

Basic information about alcohol use disorders is presented, as well as links to useful, trustworthy websites. A special and separate body of information on risky situations and craving is included (see Figure 5). In addition, an SMS text message with psychoeducational content is sent weekly to the user.

**Figure 5 figure5:**
[figure not shown]
Psychoeducation module.

#### Weekly Questionnaires

Weekly surveys are sent to patients via push technology, including a questionnaire on satisfaction with their general progress, and another regarding their craving for alcohol. Both employ Likert scales and use the previous week as a reference.

#### Weekly Feedback

Once a week, via push technology, patients receive a short feedback message of a motivational nature about their use (number of days during the last week) of the consumption recording module.

### Validation Process and Methodology

We will carry out 3 successive studies to evaluate and validate SIDEAL. All studies will recruit adults (≥18 years of age) from the outpatient clinic of the Addictions Unit of the Clinic Hospital of Barcelona. Recruitment will follow a consecutive sampling strategy. Subjects will be required to sign an informed consent form before they are recruited into any study. They will also be required to have a mobile phone with an active Internet connection. Exclusion criteria for all studies will be addiction to any other substance (excluding nicotine), cognitive decline, technological illiteracy, or any other condition precluding the use of a mobile phone.

### Feasibility Study

A 6-week pilot study will first be conducted to assess SIDEAL feasibility and usability, and users’ satisfaction. As we will have equipped the app with all features suggested in the literature to maximize feasibility, usability, and satisfaction, we expect high scores on outcome variables in this first stage. In this regard, personalization, user engagement (via push technology and weekly feedback reports), reduced invasiveness and enhanced privacy, and a high-quality user interface were of critical importance in the development of the app, and are the expected drivers of the feasibility study outcomes.

Because of the pilot nature of the study, 30 patients are considered an adequate sample size. Therefore, 30 outpatients with alcohol use disorders will be given the opportunity to install the app on their mobile phone, and will be asked to use it for 6 consecutive weeks. Inclusion criteria will be adults suffering from alcohol dependence according to DSM-IV or from severe alcohol use disorder according to DSM-V (as clinically diagnosed by their psychiatrists).

At baseline, sociodemographic data (age, sex, marital status, education level) will be collected. Clinical variables related to the disease and drinking status will also be collected at baseline and at study end, and will be taken from the Timeline Follow-Back (TLFB), which will be completed for the preceding 6 weeks at both baseline and study completion. The main variables analyzed will be the number of heavy drinking days and mean alcohol consumption in units per day. When the 6-week period is over, patients will be asked to complete an electronic questionnaire on app usability and satisfaction. The questionnaire will be an adaptation of the Usefulness, Satisfaction, and Ease-of-use Questionnaire (USE Questionnaire) [15] and will consist of 30 items to be rated by users on a 7-point Likert scale (from 0 to 6). Items are grouped into 4 main categories: usefulness, ease of use, ease of learning, and satisfaction. Extra questions about which modules were found to be most useful, and a free-text section to allow patient comments on any point they consider relevant, will be added to these items. The questionnaire data will be reported according to the Checklist for Reporting Results of Internet E-Surveys (CHERRIES) checklist [16]. Complementary data regarding usability, alcohol consumption, craving modulation, and other clinical variables will also be collected from the data generated by the app.

Statistical analysis will consist of a descriptive analysis of sociodemographic and clinical variables. Acceptance and feasibility will be analyzed as percentage of days used and through the satisfaction questionnaire, for which results will be analyzed using means and standard deviations of all respondents for each category of the questionnaire. The proportions of patients reporting high, medium, or low levels of satisfaction will also be calculated. Paired *t* tests and chi-square tests will be used for analysis of drinking variables (difference from baseline to study end). These variables will be the number of heavy drinking days and the mean number of units per day. Because of the exploratory nature of the pilot study, no regression analysis will be conducted.

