## Results

The pilot study has concluded with the inclusion of 29 patients. Results are expected to be available soon.

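### The feasibility study names chi-square tests for within-patient change in two numeric drinking variables; an ordinary chi-square test fits neither the pairing nor the variables.

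*Protocol article*

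**What the plan says.** All of this is in the Feasibility Study section of the protocol article, except where noted.

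- **Design.** One group of outpatients, no comparator, 6 weeks of app use. Drinking comes from the Timeline Follow-Back, "which will be completed for the preceding 6 weeks at both baseline and study completion". Every patient therefore supplies a before value and an after value.
- **Tests.** The sentence opens with *Paired t* and continues "tests and chi-square tests will be used for analysis of drinking variables (difference from baseline to study end".
- **Variables.** The next sentence closes the list: "These variables will be the number of heavy drinking days and the mean number of units per day". No categorical drinking variable is defined for this study.
- **Size.** "Because of the pilot nature of the study, 30 patients are considered an adequate sample size". The Results section reports the actual number: "The pilot study has concluded with the inclusion of 29 patients". Outcome results were still pending.
- **Standing.** The stated aim is feasibility: "A 6-week pilot study will first be conducted to assess SIDEAL feasibility and usability, and users’ satisfaction". The drinking analysis is exploratory: "Because of the exploratory nature of the pilot study, no regression analysis will be conducted".

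**The concern.** The paired *t* test matches both the data structure and the scale of the two variables. The chi-square test matches neither.

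1. **Scale.** A number of days and a mean number of units are numeric. A chi-square test needs categories, and the section supplies none.
2. **Pairing.** Suppose a status such as any heavy drinking (yes/no) were derived. A chi-square test of baseline against study end treats 29 patients measured twice as two independent groups of 29. Cross-tabulating each patient's baseline status against end status instead asks whether the two are associated, not whether the proportion changed.

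At stake are the p values that the pilot will report for change in drinking. The article states this choice outright, so the point is not one of detail left to a fuller document.

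**Working it through.** The documents give no alpha, power or p value for the feasibility study, so there is no figure of the plan's own to reproduce. From the documents: 29 patients included (30 planned), two measurements each. Assumed: a binary status, 60% positive at baseline, two-sided 5%, and a latent bivariate normal correlation of 0.5 or 0.7 between a patient's two values.

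**Step 1: why the level is wrong.** With no change and prevalence p, the difference in proportions has variance 2p(1 − p)(1 − φ)/n, where φ is the within-patient correlation of the binary values. The ordinary chi-square test uses 2p(1 − p)/n. Its true size is therefore approximately 2[1 − Φ(1.96/√(1 − φ))].

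- Latent correlation 0.5: the probability of being positive both times is 0.439, so φ = (0.439 − 0.36)/0.24 = 0.33. Size ≈ 2[1 − Φ(2.39)] = 1.7%.
- Latent correlation 0.7: the probability is 0.478, so φ = (0.478 − 0.36)/0.24 = 0.49. Size ≈ 2[1 − Φ(2.74)] = 0.6%.

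**Step 2: values at n = 29,** from summing multinomial probabilities over every possible 2 × 2 paired table:

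| | Latent correlation 0.5 | Latent correlation 0.7 |
|---|---|---|
| Size, ordinary chi-square | 1.5% | 0.6% |
| Size, McNemar uncorrected | 4.3% | 4.6% |
| Size, McNemar exact | 2.1% | 1.6% |
| Power 60% → 35%, ordinary chi-square | 47% | 46% |
| Power 60% → 35%, McNemar exact | 50% | 59% |
| Power 60% → 35%, McNemar uncorrected | 60% | 71% |

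Simulation of the same scenario gave powers of 48%/46%, 51%/59% and 61%/71% for the three tests, within about one point.

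**Step 3: one table.** Take 30 patients: 15 positive both times, 8 improving, 1 worsening, 6 negative both times. That is 23/30 before and 16/30 after.

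- Ordinary chi-square: pooled proportion 39/60 = 0.65; (7/30)² / (0.65 × 0.35 × 2/30) = 3.59, p = 0.058.
- McNemar: (8 − 1)²/(8 + 1) = 5.44, p = 0.020. Exact: 2 × (1 + 9)/2⁹ = 0.039.

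**Step 4: the cross-tabulation.** Take an invented table with 14 positive both times, 4 improving, 4 worsening and 8 negative both times. The proportion is 18/30 at both visits, so there is no net change. The association chi-square is 30(14 × 8 − 4 × 4)²/(18 × 12 × 18 × 12) = 5.93, p = 0.015. It is significant, but for a different question.

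**Step 5: direction.** If heavy drinking days were instead pooled over patients (30 patients × 42 days per period), the error can reverse. In one assumed scenario (logit-scale standard deviations of 1.0 between patients and 0.7 for individual change) simulation gave about 20% false positives at a nominal 5%.

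**The case against.** **The label may be loose.** The word *Paired* can be read as governing both tests, and McNemar's test is itself a chi-square test for paired proportions. This stands as a possibility. The text does not say it, however, and even on that reading no categorical variable is defined to which the test could apply.

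**The harm is computed for an endpoint the plan does not contain.** This is correct. The 60%, the 35% and the correlations are assumptions. They show what an ordinary chi-square test would do if a status were dichotomised; they do not show that any reported p value is wrong.

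**The gain from McNemar's test is easily overstated.** A reader might set 47% to 46% against 60% to 71% and infer a gain of 13 to 25 percentage points. With only about 9 to 11 discordant pairs expected at latent correlation 0.5, and 7 to 9 at 0.7, the exact test would often be chosen. Its gain is about 3 points at 0.5 and 13 at 0.7, and its own size is about 2%.

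**The impact is small.** This also stands. The pilot is about feasibility, its drinking analysis is exploratory, and both numeric variables already have a paired *t* test. A reader might infer that the efficacy conclusions are at risk. The Randomized Controlled Trial section does not support that: it uses regression and logistic models, and its sample size paragraph does not refer to the pilot's drinking results.

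**Conclusion.** The point holds in limited form. On the plain reading, the named chi-square test fits neither the two numeric variables nor the before-after design. If it were applied to a dichotomised status at patient level, its p values would be too large under positive within-patient correlation: true size about 1.5% to 0.6% instead of 5%, under the assumed 60% prevalence and latent correlation of 0.5 to 0.7.

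Two stronger readings are not supported. First, one might infer that the test would produce a false claim of benefit. At patient level the comparison of time points errs the other way, and the article does not say that days will be pooled. Second, one might infer that confidence intervals would be too wide, but the section plans no interval for change in drinking. The consequence is confined to p values in an exploratory analysis of 29 patients, and the randomized trial is untouched.

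**What to change.** In the statistical paragraph of the Feasibility Study section, delete the chi-square test for number of heavy drinking days and mean units per day, and keep the paired *t* test. If a dichotomised drinking status is to be compared between baseline and study end, define it there and name McNemar's test, in its exact form when discordant pairs are few. If a paired chi-square was meant all along, saying so and naming the variable settles the matter.

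The cost is one line of text and one line of analysis. The data are already collected and the results were not yet reported, so the change can be made before the p values are published.
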